### Diagnostic interview and symptom severity

#### Montgomery–Åsberg Depression Rating Scale (MADRS)

Study participants are evaluated with the MADRS at the screening and baseline visits to assure the score is ≥ 26, according to inclusion criteria and at RCT and post-RCT visits. The MADRS is a frequently used and well-validated clinician-administered questionnaire consisting of 10 items assessing the following depressive symptoms: apparent sadness; reported sadness; inner tension; reduced sleep; reduced appetite; concentration difficulties; lassitude; inability to feel; pessimistic thoughts; and suicidal thoughts. All of the items are rated from 0 to 6. The clinician must decide whether the rating lies on the defined scale steps (0, 2, 4, 6) or between them (1, 3, 5). This clinician-rated scale allows assessment of the severity of depressive symptoms. The total score is in the range of 0–60 and the higher the global score, the more serious the depressive symptoms. It is designed to be sensitive to change resulting from antidepressant therapy [49]. Internal rater consistency is controlled by having all trained clinician researchers complete rating scales based on standard video interviews.

#### Mini-International Neuropsychiatric Interview (MINI)

The diagnosis of MDD is confirmed using the MINI during the screening visit. The MINI is a widely used structured diagnostic interview which enables clinicians to make diagnoses of psychiatric disorder [50, 51]. It is a clinician-administered questionnaire divided into modules corresponding to diagnostic categories (MDD, suicidality, bipolar disorder, panic disorder, agoraphobia, social phobia, obsessive-compulsive disorder, post-traumatic stress disorder, alcohol dependence/abuse, substance dependence/abuse, psychotic disorder and mood disorder with psychotic features, anorexia nervosa, bulimia nervosa, generalised anxiety disorder, antisocial personality disorder). The diagnosis of MDD is confirmed if participants experience five or more of nine symptoms (depressed mood, loss of interest, significant weight loss or gain or decrease or increase in appetite, insomnia or hypersomnia, psychomotor agitation or retardation, fatigue or loss or energy, feelings of worthlessness or excessive or inappropriate guilt, diminished ability to think or concentrate or indecisiveness, recurrent thoughts of death or recurrent suicidal ideation without a specific plan or suicide attempt or a specific plan) including depressed mood or loss of interest.

#### Columbia-Suicide Severity Rating Scale (C-SSRS)

The C-SSRS is a widely used clinician-administered questionnaire for assessment of suicidal ideation or behaviour of participants [52]. It consists of a series of questions assessing suicide ideation, action taken to prepare for suicide and whether participants attempted suicide or began a suicide attempt.

### Functioning

#### National Adult Reading Test (NART)

The NART is used to estimate premorbid intelligence [53]. It consists of a list of 50 irregularly pronounced words in order of increasing difficulty. The participants have to read aloud down this list of words and the number of pronunciation errors is recorded. The clinician has previously been familiarised with all the words before administering the test.

#### Clinical Global Impression scale (CGI)

The CGI scale is an easy tool to quantify patient progress and treatment response over time. It assesses the clinician’s view of patient global functioning at baseline and after initiation of treatment. The CGI has two components: the CGI-Severity, which rates illness severity, and the CGI-Improvement, which rates change from baseline [54].

#### Functioning Assessment Short Test (FAST)

The FAST is a clinician-administered questionnaire referring to the last 15 days before assessment. It consists of 24 items divided among the following six areas of functioning: autonomy; occupational functioning; cognitive functioning; financial issues; interpersonal relationships; and leisure time. All of the items are rated from 0 (no difficulty) to 3 (severe difficulty); the higher the global score, the more serious the difficulties [55].

#### WHO-5 Well-Being Index

The WHO-5 Well-Being Index is a short, self-administered questionnaire that measures current mental well-being of participants. It consists of five items related to mood, vitality and general interests. It is a reliable measure of emotional functioning and a good screening tool for depression [56].

### Work productivity

#### Endicott Work Productivity Scale (EWPS)

The EWPS is a self-administered questionnaire assessing work productivity. It consists of 25 items and measures presenteeism and the frequency of productive behaviours during the previous week. All the items are rated from 0 (‘never’) to 4 (‘almost always’). The score of all scores is computed and the higher the global score, the worse the work productivity [57].

#### Work Limitation Questionnaire (WLQ-25)

The WLQ-25 is a self-administered questionnaire used to measure the impact of MDD on work performance. Is consists of 25 items divided among four areas: time demands; physical demands; mental/interpersonal demands; and output demands. For each item, the participant has to rate the amount of time he/she experienced difficulty (from ‘never’ to ‘always’) in the two most recent weeks [57].

#### Sheehan Disability Scale (SDS)

The SDS assesses functional impairment in the three following domains: work/school; social; and family life. It is a brief self-report tool in which the participant has to rate the extent to which he experienced disability and impairment in those domains from 0 (not at all) to 10 (extremely) during the past week. Additional questions estimate the frequency of unproductivity at school/work [57].

### Cognitive assessment (THINC-it tool)

The THINC-it tool has been developed to screen for cognitive dysfunction in patients with MDD. The tasks are consistently delivered in the following order: Spotter; Symbol Check; Codebreaker; and Trails, with a clinician blinded to treatment group instructing participants to read the tutorial instructions preceding each of the THINC-it tasks [58]. In addition, Perceived Deficits Questionnaire-5-D (PDQ-5-D) is administered to all participants. PDQ-5-D is a five-item auto-questionnaire measuring subjectively reported cognitive deficits.

#### Spotter

The Spotter test is used to assess attention and speed of response. In this test, participants are instructed to respond by pressing keys on the left- or the right-hand side of the keyboard corresponding to the direction to which an arrow on the screen is pointing.

#### Symbol Check

The Symbol Check test measures working memory and attention skills. In this test, the participant is presented a series of stimuli at a constant rate. The task is to map the currently presented stimulus on arrow keys of a keyboard to one they have recently seen in the stream (one position back).

#### Codebreaker

The Codebreaker test, which is modelled on the digit symbol substitution test (DSST), measures attention, perceptual speed, motor speed, visual scanning and memory. It requires the examinee to transcribe a unique geometric symbol with its corresponding number. The examinee is initially shown a key containing the numbers from 1 to 6. Under each number, there is a corresponding geometric symbol. The participant is then shown a series of numbers on the screen and asked to match the number with the corresponding geometric symbol.

#### Trails

The Trails test is designed to test elements of executive function. Participants are instructed to connect a set of 18 dots as fast as possible while still maintaining accuracy. It can provide information about visual search speed, scanning, speed of processing, mental flexibility, as well as executive functioning.

## Blood analysis

A blood test is taken during the screening visit for measuring CRP levels, for the allocation into the ‘Depression with inflammation’ and ‘Depression without inflammation’ strata of the study. Another blood test to measure haemoglobin and a pregnancy test in premenopausal women is performed at the same time. Anti-inflammatory medication is associated with higher risk of GI bleeding [59] and haemoglobin levels have been suggested as a relevant marker of GI damage [60]. Therefore, measuring haemoglobin levels before treatment allows detection of potential pre-existing GI damages. If haemoglobin levels are abnormal, participants are referred to their treating doctor before starting the treatment. The pregnancy test is performed since vortioxetine is classified as a category B3 drug in Australia, meaning that studies in animals have shown evidence of an increased occurrence of fetal damage, the significance of which is considered uncertain in humans. Pregnant women therefore are not eligible for this trial. Blood tests are also performed at the baseline visit, after six weeks of treatment and at the six-month post-trial visit for analyses of serum inflammatory proteins (TNF-α, IL-6 and IL-1β). The blood sample is collected earlier (at last observation) if participants withdraw from the study. The storage of biospecimens is split between different secured freezers at the Adelaide Psychiatric Biomarker Centre at the Discipline of Psychiatry, University of Adelaide, the Adelaide Health and Medical Sciences building, all of which are monitored by a central alert system 24 h/day seven days a week.

## Results analysis

The primary outcome (change in MADRS score from baseline to week 6) will be analysed using a mixed effects model for repeated measurements (MMRM, all available data), with freely varying mean and covariance structures. Treatment will be included as fixed factors. The baseline CRP level and stratified group (‘Depression with inflammation’ versus ‘Depression without inflammation’) will be controlled for. The existence of an interaction between inflammation at baseline and treatment will be assessed, recognising that the study is only powered to detect very large interaction effects. As previously recommended, ANCOVA will be used to account for possible baseline imbalance between treatment arms, thus allowing for participant differences [61]. As previously stated, we hypothesise that a reduction in MADRS score will be higher in participants receiving vortioxetine plus celecoxib in the ‘Depression with inflammation’ stratum compared to participants receiving the same treatment in the ‘Depression with no inflammation’ stratum. The potential treatment effect on CRP will be separated into the stratified strata (‘Depression with inflammation’ versus ‘Depression without inflammation’) as well as for the total group (all four groups). For dichotomous endpoints, such as response and remission, logistic regression with treatment as a factor and the baseline score as a covariate will be used. For continuous endpoints, the same methodology as that described for the primary endpoint will also be used. Continuous endpoints will also be analysed using observed case (OC) and last observation carried forward (LOCF), with LOCF being used to account for missing data and to perform sensitivity analysis. Association between function (FAST, Work Limitations Questionnaire and Sheehan Disability Scale) and endpoints addressing cognitive dysfunction will be explored by means of a partial correlation coefficient. Adverse events and the CSSR-S will be summarised using descriptive statistics.

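### The covariates listed for the primary MMRM omit baseline MADRS, and the plan does not say whether the ANCOVA for baseline imbalance is part of that model or a separate analysis

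*Protocol article*

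**What the plan says.** All the analysis statements are in the Results analysis section of the protocol article.

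- **Primary outcome and model:** "The primary outcome (change in MADRS score from baseline to week 6) will be analysed using a mixed effects model for repeated measurements". The model uses all available data and leaves the mean and covariance structures free.
- **Terms in the model:** "Treatment will be included as fixed factors", and "The baseline CRP level and stratified group (‘Depression with inflammation’ versus ‘Depression without inflammation’) will be controlled for". A treatment-by-inflammation interaction is also to be assessed. Baseline MADRS is not mentioned.
- **Baseline imbalance:** "ANCOVA will be used to account for possible baseline imbalance between treatment arms, thus allowing for participant differences". The sentence gives no outcome, covariate, analysis set or rank.
- **Binary endpoints, for contrast:** "logistic regression with treatment as a factor and the baseline score as a covariate will be used".
- **Other continuous endpoints:** these follow the primary endpoint's method, with observed-case and LOCF analyses in addition.

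The Objectives section and Table 1 place the primary hypothesis in participants with baseline CRP > 3 mg/L.

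**The concern.** The article does not simply leave the primary model to a later plan. It lists the adjustment variables, omits the baseline value of the outcome, and then hands the job of that covariate to a method with a different name. The logistic model in the same section does name the baseline score, so a reader may take its absence from the MMRM list as deliberate.

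Two readings are open:

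1. ANCOVA means baseline adjustment within the MMRM. The MMRM's covariate list is then incomplete.
2. ANCOVA is a separate analysis. The primary MMRM then compares unadjusted change, which is less precise and moves with any chance imbalance in baseline MADRS. A second estimate also exists, with nothing to say which one decides.

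The uncertainty carries over to every other continuous endpoint, because those borrow the primary endpoint's method.

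**Working it through.** The plan gives no figure on this point. Its sample-size statement (effect size 0.25, power 0.95, alpha 0.05, 50 per group) contains no SD and no baseline-to-week-6 correlation. The calculation below takes the second reading, with a single time point standing in for the MMRM.

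**Inputs**
- Assumed, not in the document: baseline SD sb = 4–7, week-6 SD s6 = 8–9, correlation r = 0.3–0.5. Entry at MADRS ≥ 26 (Inclusion and exclusion criteria) truncates the baseline distribution, which makes the lower values of sb plausible.
- From the document: 50 per arm within a stratum, 100 per arm over both strata.

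**Step 1. Variance per patient**

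Unadjusted change: sb² + s6² − 2·r·sb·s6. Baseline-adjusted: s6²·(1 − r²).

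| sb, s6, r | Change | Adjusted | Reduction from adjusting |
|---|---|---|---|
| 4, 9, 0.3 | 16 + 81 − 21.6 = 75.4 | 81 × 0.91 = 73.7 | 2.2% |
| 5, 9, 0.4 | 25 + 81 − 36 = 70.0 | 81 × 0.84 = 68.0 | 2.8% |
| 5, 8, 0.5 | 25 + 64 − 40 = 49.0 | 64 × 0.75 = 48.0 | 2.0% |
| 7, 9, 0.4 | 49 + 81 − 50.4 = 79.6 | 68.0 | 14.5% |

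Taken the other way, the last row means that the unadjusted variance is 79.6/68.04 − 1 = 17% larger than the adjusted one. In the first three rows it is 2–3% larger.

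**Step 2. Shift from a one-standard-error chance imbalance in baseline MADRS**

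Shift = (1 − b)·sb·√(2/n), with b = r·s6/sb and n per arm.

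- n = 50, √(2/50) = 0.2. Smallest case (5, 8, 0.5): b = 0.80, shift 0.20 × 5 × 0.2 = 0.20 points. Largest case (7, 9, 0.4): b = 0.514, shift 0.486 × 7 × 0.2 = 0.68 points. The unadjusted standard error, √(variance × 2/50), is 1.40 and 1.78 in these two cases.
- n = 100, √(2/100) = 0.141. The shifts become 0.14 and 0.48 points, with standard errors of 0.99 and 1.26.

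**Step 3. Type I error if either result could be claimed**

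Under the null, the two test statistics correlate at √(adjusted variance / change variance), which is 0.989, 0.986, 0.990 and 0.925 for the four rows. The bivariate normal probability that at least one exceeds 1.96 in absolute value is 5.7%, 5.8%, 5.7% and 6.8%.

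**Cross-check with other assumptions.** A simulation with equal baseline and week-6 SDs and r = 0.2–0.7 (8,000 null trials per setting) gave an either-significant rate of about 7–8%, and opposite verdicts in about 4–6% of trials. Equal SDs take no account of the narrowing at entry, so I rely on the lower figures.

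**The case against.** The strongest reply is that the article describes a single primary method. Only the MMRM is tied to the primary outcome. The ANCOVA sentence states a purpose rather than an outcome or visit, and the section later refers to the primary endpoint's methodology in the singular. A reader might infer that the plan sets up two primary analyses that both answer the primary question. The text does not support that. It is equally consistent with covariate adjustment inside the MMRM.

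A reader might also infer that the two methods would use different patients, with ANCOVA on completers or LOCF values and the MMRM on all visits. That too is not stated. No analysis set is given for the ANCOVA. Observed-case and LOCF analyses are introduced separately, and LOCF is tied to missing data and sensitivity analysis.

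Two points about size also stand. The shift from chance imbalance is not bias under randomisation, since the standard error already covers it. The type I inflation arises only if someone picks the better result, which the text does not authorise.

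It can also be said that covariate lists belong in the analysis plan. That would answer silence, but this section gives a list, leaves out baseline MADRS and names another method for its job. Either reading leaves wording to correct.

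**Conclusion.** The point holds as a fault in how the primary model is specified. As listed, the primary MMRM does not adjust for baseline MADRS, and the place of the ANCOVA is undefined.

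The consequence is modest. If the ANCOVA is separate, leaving baseline MADRS out of the primary model forgoes a variance reduction of 2–3% at a baseline SD of 4–5 and about 15% at SD 7. Free choice between the two results would put type I error at roughly 5.7–6.8%. All these figures depend on assumed SDs and correlations and on a single-time-point approximation. If the ANCOVA sentence means adjustment within the MMRM, none of these costs arises and only the wording is at fault. The change is worth making because it is cheap and removes the doubt on either reading.

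**What to change.** Replace the separate statements with one primary model:

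- An MMRM of MADRS change at weeks 2, 4 and 6 with treatment, visit and treatment-by-visit. Keep the covariates already listed (CRP stratum and baseline CRP level), and add baseline MADRS and baseline MADRS-by-visit.
- Name one primary test: the week-6 treatment contrast in participants with CRP > 3 mg/L, to match the primary hypothesis. This needs treatment-by-stratum terms at each visit, or a fit within that stratum. A contrast pooled over both strata would not match the hypothesis.
- Delete the separate ANCOVA, or label it supportive and state its outcome, covariates and patients.

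The cost is wording only. Baseline MADRS is measured on every participant as an entry criterion, and symptom severity is already assessed fortnightly during the RCT period.

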Secondary hypothesis	A larger reduction of circulating levels of the inflammatory marker CRP will be observed in the group of depressed patients who are treated with antidepressant plus anti-inflammatory medication	A larger reduction of circulating levels of the inflammatory marker CRP will be observed in the group of depressed patients who are treated with vortioxetine plus celecoxib 400 mg
Secondary objective 2	To test whether there is evidence of a different effect of the combined treatment in the two inflammation strata	To test whether there is evidence of a different effect of the combined treatment with vortioxetine and celecoxib 400 mg in the two inflammation strata
Secondary objective 3	To investigate the safety of the anti-inflammatory treatment when combined with antidepressant	To investigate the safety celecoxib 400 mg treatment when combined with vortioxetine
Secondary objective 4	To investigate the effects of the antidepressant on cognition, psychosocial and workplace performance measures in MDD	To investigate the effects of vortioxetine on cognition, psychosocial and workplace performance measures in MDD

The secondary objectives of the study are:To investigate the anti-inflammatory effects of a combined treatment of MDD with vortioxetine and celecoxib in individuals with baseline inflammation (CRP levels > 3 mg/L) over a six-week period. We aim to demonstrate a larger reduction of circulating levels of the inflammatory marker CRP in the group of depressed patients who are treated with antidepressant plus anti-inflammatory medication (see Table 1).To test whether there is evidence of a different effect of the combined treatment in the two inflammation strata, although the study is not powered to detect this effect (see Table 1).To investigate the safety of the anti-inflammatory treatment of celecoxib 400 mg when combined with vortioxetine (see Table 1).To investigate the effects of vortioxetine on cognition (using the THINC-It tool) and on psychosocial and workplace performance measures in MDD (see Table 1).

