### Recruitment and study design

A total of 200 patients with MDD will be included in the study. Recruitment and treatment take place in the wider Central Adelaide Local Health Network (CALHN), with all participant appointments being held in the Clinical Research Facility in the Health and Medical Sciences Building, Discipline of Psychiatry, University of Adelaide. In addition to this, and to ensure that required numbers of study participants are recruited, people from the general population who meet the inclusion criteria are able to engage with the proposed study, as it is made available through advertisement. Participants are free to withdraw from the study at any time.

The study is designed as a parallel group RCT with a superiority framework, investigating 200 participants with MDD over six weeks in the primary phase followed by a six-month post-RCT follow-up period (Fig. 1). The study proposes to measure the inflammatory marker CRP before the commencement of treatment. Following CRP measurement, study participants are then assigned into one of two study strata based on CRP levels. The first of these study strata is made up of 100 individuals with CRP levels > 3 mg/L (the ‘Depression with inflammation’ stratum) and the second study stratum is an active control, made up of 100 individuals with CRP levels ≤ 3 mg/L (the ‘Depression without inflammation’ stratum). In each stratum, participants are randomly allocated in a 1:1 ratio to augmentation of vortioxetine antidepressant treatment with either celecoxib or placebo. Following six weeks of concomitant administration of celecoxib or placebo with vortioxetine, the celecoxib or placebo is then stopped and the participants are treated with vortioxetine only for an additional two weeks. This allows the opportunity to assess the efficacy of taking vortioxetine alone. While the primary time point is the six weeks in which we compare vortioxetine with augmentation against vortioxetine without augmentation, following the RCT phase, all participants have the opportunity to continue on vortioxetine without celecoxib or placebo for another six months during a post-RCT observational study period.

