### Study sample size

Given a power of 0.95, and an alpha error of 0.05, the study sample size required to detect a change in MADRS of an effect size of 0.25 between baseline and week 6 would be 50 study participants in each of the four groups. This would be a total of 200 study participants (100 participants in the ‘Depression with inflammation’ stratum and 100 study participants in the ‘Depression without inflammation’ stratum; 50 participants in each treatment group, respectively).

We have found in our internal analyses that around 40–50% of individuals have a CRP level of > 3 mg/L, so we expect to be able to recruit 100 participants to the ‘Depression with inflammation’ stratum and 100 participants to the ‘Depression without inflammation’ stratum. The proposed study duration is two years, which will allow time to recruit the required number of study participants.

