## Discussion

Abundant literature has highlighted that inflammation is closely associated with depressive symptoms in patients with MDD [6, 13, 24, 62–65]. Targeting inflammation has therefore become a promising strategy in improving depressive symptoms. Interestingly, numerous studies demonstrate a beneficial effect of anti-inflammatory medications (e.g. NSAIDs or anti-cytokines) on depressive symptoms in patients with MDD [34, 36, 38]. Specifically, administering COX-2 inhibitors such as celecoxib in addition to antidepressant treatment for six or eight weeks improves treatment response and remission in comparison to antidepressant medication alone [48].

According to this literature, identifying individuals with depression and inflammation could therefore help in developing new personalised treatment for MDD. However, to our knowledge, there is no previous study assessing the therapeutic effect of administering anti-inflammatory medication combined with antidepressant medication on the basis of raised inflammatory markers at baseline. Through the RCT we propose, we will be able to investigate the effectiveness of using a simple blood test, before treatment of depression, to guide the use of anti-inflammatory medication as an addition to antidepressant medication in patients with depression and inflammation. Indeed, if the efficacy of augmenting vortioxetine with celecoxib 400 mg is higher in participants with inflammation at baseline compared to participants with no inflammation at baseline, it would be recommended to use this augmentation strategy only in MDD patients with raised inflammation before treatment.

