The primary outcome of this study will be MADRS score. It is expected that antidepressant combined with anti-inflammatory medication will reduce MADRS score by 50% from baseline to six weeks (end of treatment) in the ‘Depression with inflammation’ stratum of the study. We also expect that the reduction in MADRS score in the ‘Depression with inflammation’ stratum will be larger among those for whom vortioxetine treatment has been augmented with celecoxib than those in the same stratum receiving vortioxetine and placebo. Furthermore, the MADRS score reduction in the former group will also surpass that achieved by both treatment groups in the ‘Depression with no inflammation’ stratum. CRP level as a secondary outcome measure is expected to be reduced by 50% between baseline and six weeks in the group treated with antidepressant and anti-inflammatory medication in the ‘Depression with inflammation’ stratum of the study and is not expected to change in the group treated with antidepressant only in the same stratum. Similarly, CRP levels are not expected to be changed following both treatments in the ‘Depression with no inflammation’ stratum. Secondary outcome measures also include other inflammatory markers (TNF-α, IL-6 and IL-1β), levels which are expected to be reduced by 50%. In addition, a 50% improvement in cognitive dysfunction, functional measures and workplace functioning is expected. Finally, this study also assesses the safety of the anti-inflammatory celecoxib 400 mg when combined with vortioxetine by measuring potential side effects at each visit.

It is hypothesised that primary and secondary outcome measures will not show a statistically significant difference between participants receiving vortioxetine only and participants receiving vortioxetine plus celecoxib within the ‘Depression with no inflammation’ stratum of the study.

In summary, we anticipate that the results of this trial will allow the development of a decision aid for depression medication, thus improving treatment response and remission, especially in patients suffering from recurrent treatment resistant depression.

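### The CRP hypotheses are written as contrasts that cannot show that CRP predicts benefit from celecoxib, and the recommendation to augment only in raised inflammation is not tied to the planned interaction test

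*Protocol article*

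**What the plan says.** Four sections of the protocol article bear on whether CRP predicts benefit from celecoxib.

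- **Objectives.** The primary hypothesis compares combined treatment with antidepressant alone within the CRP > 3 mg/L stratum, and no difference is hypothesised in the low stratum. Secondary objective 2 asks whether the effect of combined treatment differs between strata, "although the study is not powered to detect this effect".
- **Recruitment and study design.** CRP sets the stratum; participants are then randomised 1:1 to celecoxib or placebo within it. The framework is superiority. The section says that "the second study stratum is an active control".
- **Results analysis.** A treatment-by-inflammation interaction will be assessed, with a caution that only very large interactions are within reach. The section then claims to repeat the hypothesis given earlier, but words it as a larger MADRS reduction with celecoxib in the high-CRP stratum "compared to participants receiving the same treatment in the ‘Depression with no inflammation’ stratum".
- **Discussion.** The high-CRP celecoxib group is expected to improve more than either low-CRP group. In the low stratum, outcomes "will not show a statistically significant difference between participants receiving vortioxetine only and participants receiving vortioxetine plus celecoxib". If augmentation is more efficacious with inflammation than without, "it would be recommended to use this augmentation strategy only in MDD patients with raised inflammation before treatment".

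**The concern.** The Objectives and Results analysis present two different comparisons as one hypothesis. The first is randomised. The second sets two celecoxib groups side by side whose only designed difference is CRP, which nobody allocated. Any difference between them is the sum of how the two kinds of patient would have fared anyway and how much celecoxib helped each. The same is true of the Discussion's comparison of the high-CRP celecoxib group with both low-CRP groups.

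Predicting a non-significant result in the low stratum has a different weakness. In a superiority trial with no stated margin, non-significance is compatible with a worthwhile effect, so it cannot establish that celecoxib does nothing there.

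What is at stake is the trial's headline message. A recommendation restricted to raised inflammation needs evidence that the treatment effect differs by CRP. The article plans the test that could give this evidence but does not say that the recommendation depends on it.

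**Working it through.** **Inputs.** From Study sample size: "Given a power of 0.95, and an alpha error of 0.05"; the aim to "detect a change in MADRS of an effect size of 0.25 between baseline and week 6"; "50 study participants in each of the four groups". From the Celecoxib section: a cited add-on effect of 0.82 (standardised mean difference). Assumed here: outcome SD = 1, two-sided test (sidedness is not stated), no dropout, and no gain from covariates or repeated measures. Normal approximation unless stated.

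**1. The plan's own figure.** It is not reproduced exactly. Read as a standardised difference of 0.25 between two arms, 95% power needs 416 per arm, and 50 per arm give power 0.24. The closest of the readings tried is Cohen's f = 0.25 with 1 df and all 200 participants pooled: N = 210, with power 0.94 at 200. Nothing below depends on this figure except the 50 per cell.

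**2. The celecoxib/high versus celecoxib/low contrast.** Write the mean improvement in each cell as the stratum's prognosis plus, under celecoxib, a treatment effect.

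- Celecoxib/high − celecoxib/low = (prognosis high − prognosis low) + (effect high − effect low).
- Interaction = (celecoxib − placebo in high) − (celecoxib − placebo in low) = effect high − effect low.

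Only the second removes prognosis. For illustration, if this contrast were tested at 50 v 50, SE = √(2/50) = 0.20 SD. With no interaction at all, an assumed prognostic difference of 0.1, 0.25 or 0.5 SD would give a significant result with probability 0.08, 0.24 or 0.71 (0.70 at 0.5 SD by noncentral t).

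**3. Non-significance in the low stratum.** SE = 0.20 SD, so the 95% CI half-width is 1.96 × 0.20 = 0.39 SD. Power is w = Φ(D/0.20 − 1.96). A true effect of 0.25 SD is missed with probability 1 − 0.239 = 0.76, and one of 0.5 SD with probability 1 − 0.705 = 0.29.

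**4. Significant in high, non-significant in low, when the true effect D is the same in both.** The strata are independent, so the probability is w(1 − w).

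| D (SD) | w | w(1 − w) |
|---|---|---|
| 0.25 | 0.239 | 0.18 |
| 0.40 | 0.516 | 0.25 |
| 0.50 | 0.705 | 0.21 |
| 0.82 | 0.984 | 0.02 |

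**5. The valid test.** The interaction has SE = √(4/50) = 0.283 SD and power Φ(Δ/0.283 − 1.96), where Δ is the difference between strata in the celecoxib effect.

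- Δ = 0.25 SD: 0.14. Δ = 0.5 SD: 0.42. Δ = 0.82 SD: 0.83.
- Detectable at 80% power: (1.96 + 0.842) × 0.283 = 0.79 SD. At 95% power: (1.96 + 1.645) × 0.283 = 1.02 SD.
- Needed for 80% power: 4 × (2.802/Δ)², about 126 per cell for Δ = 0.5 SD and 503 for Δ = 0.25 SD.

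**6. Sensitivity.** Baseline adjustment with an assumed correlation of 0.5 multiplies every SE by √(1 − 0.25) = 0.87. The 80% detectable interaction becomes 0.79 × 0.87 = 0.69 SD. The reasoning in step 2 is unaffected.

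**The case against.** A reader might infer that the claim that CRP guides treatment is to rest on the comparison of the two celecoxib groups and on non-significance in the low stratum. The documents do not support that.

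- The Objectives list the difference in effect between strata as a secondary objective, and Results analysis plans the interaction just before the misworded hypothesis. Both disclose its low power, so the figures in step 5 quantify an admitted limitation.
- The primary hypothesis in the Objectives is a valid randomised contrast, and the Discussion repeats it alongside the cross-stratum one.
- The Discussion's condition for its recommendation concerns the efficacy of augmenting in one stratum against the other. That reads most naturally as a difference in treatment effects.
- No section schedules a 50 v 50 test of the two celecoxib groups, so the rates in step 2 describe what such a test would do if run. The prognostic differences are assumptions. The Background links CRP to symptom severity, not to six-week change, and a prognostic difference could mask the hypothesised result as easily as mimic it.
- No section says that non-significance will be reported as equivalence. At the cited effect of 0.82 SD the misleading pattern in step 4 is rare.
- The active-control label might suggest that the low stratum is the comparator for efficacy. The same section gives each stratum its own randomised placebo arm, so this is loose terminology only.

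All of this stands and limits the point. It leaves three things unanswered: Results analysis misreports the Objectives; the stated CRP hypotheses are contrasts that cannot show prediction; and nothing makes the interaction result govern the recommendation.

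**Conclusion.** The point holds as a defect in how the hypotheses and the permitted conclusion are written. The MADRS hypothesis in Results analysis does not match the one it claims to repeat. Neither it, nor the Discussion's cross-stratum comparison, nor the predicted non-significance can show that CRP predicts benefit from celecoxib. The interaction can, but with 50 per cell it has power 0.42 for a 0.5 SD difference in effects and detects about 0.8 SD at 80% power. If the two strata were read separately instead, equal true effects of 0.25 to 0.5 SD would produce the hypothesised pattern 18–25% of the time, falling to about 2% at 0.82 SD. These sizes rest on SD = 1, a two-sided 0.05 test, full retention and no covariate gain. The logical point needs only that CRP stratum is not randomised, which the design section makes plain.

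**What to change.** 1. In Results analysis, restore the hypothesis of the Objectives: celecoxib versus placebo within CRP > 3 mg/L. State the CRP hypothesis separately, as a difference between strata in the randomised celecoxib-minus-placebo effect.
2. In the Discussion, make the recommendation restricted to raised inflammation conditional on the interaction estimate favouring that stratum, with a 95% CI that excludes zero.
3. For the low stratum, report the estimate and its 95% CI, and do not interpret non-significance as no difference. Label the comparison of the high-CRP celecoxib group with the low-CRP groups as descriptive, or remove it.
4. Optionally, stop calling the low stratum an active control.

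These are wording changes. They need no extra participants, visits or data and leave the planned interaction analysis as it is. The cost is a more cautious permitted conclusion: unless the interaction is very large, the trial will probably be unable to say that augmentation should be confined to raised inflammation.
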